### Objectives

Our overall objective is to conduct a mixed methods evaluation of a practice facilitation intervention designed to improve the primary care management of refugees in 36 general practice clinics across 3 regions: South East Melbourne (SEM), North West Melbourne (NWM) and South West Sydney (SWS).

We asked whether a facilitation-based intervention directed at improving the quality of general practice-based primary care delivered to patients with a refugee background could increase:The conduct and documentation of comprehensive physical and mental health assessments among patients identified as being from a refugee background (primary outcome)

Secondary outcomes:2.Refugee status determination and recording3.The use of credentialed interpreters among patients identified as being from a refugee-like background4.Practice staff knowledge and use of referral pathways to refugee specific health and social welfare services

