Each RPT worked to characterise each region’s policy, program and service context with particular reference to the care of refugee populations. We focused specifically on barriers and enablers affecting access, transition and quality of primary care within the region. To further understand regional partnership needs, each RPT performed a focused scientific and grey literature review, analysed secondary data extracted from the Australian Bureau of Statistics Census, Department of Home Affairs Settlement Reporting Facility, settlement agencies, public health services and local councils, and conducted a series of key informant interviews with health service managers, policy advisors and clinicians. The three RPTs then met in a deliberative forum [28] to determine priority interventions, from which four core areas of activity were chosen;Physical and mental health assessments: GPs and practice nurses will have relevant skills and knowledge to conduct comprehensive refugee physical and mental health assessments.Refugee identification: general practice clinics will have accurate and accessible mechanisms in place to record and retrieve refugee identification, status, country of birth or ethnicity, year of arrival, and need for interpreter.Use of interpreters: practices will have a practice protocol for using interpreters, and ensure that staff have appropriate knowledge and skills in their role of supporting use of interpreters**.**Referral pathways: practice staff will gain an understanding of refugee health referral pathways in the region (including available services, eligibility requirements and referral procedures).

These areas of focus helped the study objectives (see above). All practices recruited will be asked to work on these four core areas as a minimum, with the option to choose an additional 1–2 activities from a list of optional tasks depending on interest and capacity (Table 2).

**Table 2 Tab2:** Intervention Optional activities

Activity	Description
Cultural awareness	Practice staff demonstrate cultural awareness and sensitivity to refugee issues, including an understanding of the refugee experience.
Communication skills	GPs and practice nurses have appropriate communication skills (They are sensitive to the needs of refugees and take time to explain care to patients so they can make informed decisions by understanding what is happening as part of their care).

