### Sample size

Given that our primary outcome measure is a proportion i.e. the proportion of refugee patients’ records that show a refugee health assessment was billed when it was indicated, then to detect a post-intervention increase in percentage by 25–30% (a medium-large effect) we need approximately 12 clinics per region. In each of the 12 clinics we require cross-sectional data from 30 refugee background patients at each timepoint. Sample size calculations were done using Stata statistical software stepped-wedge for clusters defined at the level of the practice, intra-class correlation coefficient of 0.05, 80% power, an alpha of 0.05 and data collected at two time points [34].

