### Data collection methods

Evaluation of the impact of the intervention will be assessed at the level of the practice. The researchers will collect data from early intervention practices at three-time points: at baseline (prior to the start of the intervention), at 6-months (immediately after completion of the intervention), and at 12 months (6-months after the intervention has been completed). Data collection in the late intervention practices will follow the same schedule, however they will have an additional point of data collection immediately prior to the start of the intervention. Table 4 provides an overview of the data collection methods used at each time point.

**Table 4 Tab4:** Data Collection Timeline

	Practice Description Survey	Refugee Health Survey	Provider Survey	PENCS CAT4™ extract
Pre-intervention (Baseline)	x^a^	x	x	x
Post-intervention	–	x	x	x
6-months post intervention	–	–	–	x

^a^Late intervention group had two sets of baseline data collected; once at the initial recruitment and the other just before intervention began

A qualitative study is embedded within the quasi-experimental randomised controlled trial. We will use qualitative methods to generate an in-depth understanding of practice facilitation as the mechanism of change, and the key contextual determinants of change. Qualitative data will illuminate our understanding of variations in quantitative practice performance data in relation to refugee identification, interpreter use, conduct of comprehensive health assessments and referral, in response to the intervention.

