### Statistical methods

Changes in practice performance relating to the primary outcome measure will be assessed between early and late intervention practice groups using multilevel mixed effects models to account for clustering as recommended for stepped-wedge cRCT designs [19, 20]. All quantitative outcome measures will be assessed for clustering, and if not significant may be further explored through uni-level multivariate methods (e.g. logistic regression to investigate factors affecting the proportion of consultations with interpreter use). However, if practice-level clustering is indicated, then the mixed models will include a cluster-specific random effect to deal with clustering at the practice level. In the main analysis the independent variables defined as fixed effects will be group allocation (1 = early, 0 = late), intervention status (0 = pre-intervention, 1 = post-intervention) and timepoint (0 = baseline for all practices, 1 = post intervention for early practices, pre-intervention for late start practices, 2 = 6 months post intervention for early practices, post intervention for late start practices, 3 = 6 months post intervention for late practices). Timepoint will be included as a categorical variable. In subsequent analyses, provider and practice level covariates thought to influence outcomes will be included to adjust for baseline differences between the two groups.

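### The main model gives each practice one effect that is constant over time, so its standard error is too small if practice effects change between extracts; add a practice-by-timepoint effect for the record-extract outcomes

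*Protocol article*

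**What the plan says.** Statistical methods describes multilevel mixed effects models of the kind recommended for stepped-wedge designs. The fixed effects are group allocation, intervention status and timepoint as a category. Where practice-level clustering is indicated, "then the mixed models will include a cluster-specific random effect to deal with clustering at the practice level". No practice-by-timepoint effect, decaying correlation or robust variance is named. The practice effect is itself conditional: "All quantitative outcome measures will be assessed for clustering, and if not significant may be further explored through uni-level multivariate methods".

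The design is "36 general practice clinics across 3 regions". Sample size states "In each of the 12 clinics we require cross-sectional data from 30 refugee background patients at each timepoint" and assumes "intra-class correlation coefficient of 0.05, 80% power, an alpha of 0.05 and data collected at two time points". Only one intra-class correlation is given, with nothing on how it changes between extracts.

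Practices work on four core areas and may add one or two activities "from a list of optional tasks depending on interest and capacity". Of the embedded qualitative study, Data collection methods says "Qualitative data will illuminate our understanding of variations in quantitative practice performance data", in response to the intervention.

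**The concern.** A single practice effect, read in the ordinary way, assumes that a practice departs from the average by the same amount at every extract. Practice-specific change between extracts does not cancel from the contrast that estimates the intervention effect. The model has nowhere to put such change except the residual, where it is averaged over all records and nearly vanishes. The reported standard error then hardly changes while the true one grows. At stake are the width of the primary confidence interval and the error rate of its test, and the same for the other outcomes taken from the extracts. This does not depend on the same patients recurring across extracts; it arises even if every patient is different.

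**Working it through.** **Inputs from the article:** 36 practices; 30 records per practice and timepoint; intra-class correlation (ICC) 0.05; alpha 0.05. Early practices are observed at timepoints 0, 1, 2 (status 0, 1, 1) and late practices at 0, 1, 2, 3 (status 0, 0, 1, 1).

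**Assumptions:** 18 early and 18 late practices; equal record counts; two-sided test; total variance 1; no true effect; a range for CAC. The sample size figure cannot be reproduced because no baseline proportion is given, and nothing below uses it.

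**Step 1, the estimator.** Let D0, D1, D2 be the early-minus-late differences in means at timepoints 0, 1 and 2. The group term absorbs a constant difference, and the timepoint 3 term absorbs the late-only extract. Status differs between groups only at timepoint 1, so the estimate is D1 − (D0 + D2)/2. Constant practice effects cancel. With w the variance of a practice-timepoint mean around the practice's own level, the variance is (w/18 + w/18)(1 + 1/4 + 1/4) = w/6.

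**Step 2, the true w.** w = (1 − ICC)/m + ICC(1 − CAC). At m = 30 and CAC 0.8: 0.95/30 + 0.01 = 0.0417. True standard error: √(0.0417/6) = 0.0833 SD.

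**Step 3, the w the planned model uses.** There are 18×3 + 18×4 = 126 practice-timepoints. That gives 126×29 = 3654 degrees of freedom within them and 126 − 36 = 90 between timepoints within practices. The pooled residual variance is about 0.95 + 90×30×0.01/(3654 + 90) = 0.9572, so w is 0.9572/30 = 0.0319. Model standard error: √(0.0319/6) = 0.0729 SD.

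**Step 4, type I error.** The ratio of standard errors is 0.0729/0.0833 = 0.875. Then 2(1 − Φ(1.96 × 0.875)) = 8.6%. At CAC 1 the two standard errors agree (0.0726) and the article's alpha of 5.0% is recovered.

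**Step 5, the range at ICC 0.05.**
- 30 records: 5.9% at CAC 0.95, 6.8% at 0.9, 8.6% at 0.8, 13.9% at 0.5.
- 10 records: 5.3% at 0.95, 6.1% at 0.8, 7.8% at 0.5.
- 100 records (an assumed count): 8.1% at 0.95, 11.2% at 0.9, 17.0% at 0.8.

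With 30 records and CAC 0.8, the ICC also matters: 6.4% at ICC 0.02 and 12.6% at ICC 0.10.

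**Step 6, simulation at 30 records and ICC 0.05.** A linear model (2000 runs per setting) gave 5.0%, 6.1%, 7.1%, 9.1% and 14.8% at CAC 1, 0.95, 0.9, 0.8 and 0.5. A random-intercept logistic model with a 30% null rate (1500 runs) gave 4.9%, 5.3%, 6.7%, 6.9% and 11.4%. A separate logistic simulation (500 runs) gave 8.0% at CAC 0.8.

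**Step 7, in percentage points.** For a 40% outcome the SD is √(0.4×0.6) = 0.49. At CAC 0.8 the correct standard error is 0.0833×0.49 = 4.1 points. With no practice-by-timepoint variation it would be 0.0726×0.49 = 3.6 points, and the planned model still reports about that.

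**The case against.** A practice random effect with categorical time is a recognised stepped-wedge model. The article does not say that this is the only random term, and an analysis plan that is not shown may say more. That limits the point, but does not remove it: the article describes its main analysis down to the random effect, and the structure it names is the narrow one.

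A reader might infer that any departure from parallel drift pushes the false-positive rate to 8% or as far as 17%. The documents do not support this. At the article's own 30 records and ICC, CAC 0.9 to 0.95 is already non-parallel drift and gives only 6% to 7%. At those inputs, 8% needs a CAC of about 0.83 and 17% one of about 0.31. The 17% at CAC 0.8 needs about 100 records, a count found nowhere in the article. Although the extract takes all matching records, the primary outcome is restricted to patients within 12 months of arrival, so its denominators may be small.

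A reader might also take the optional activities and the qualitative study as evidence that practices will drift. Those texts concern varied response to the intervention, whereas the error rates above assume no effect at all. They mainly support letting the intervention effect vary between practices. Some drift is plausible on other grounds: arrivals within 12 months turn over between extracts 6 months apart, and practices with rolling start dates share a timepoint in different calendar months. The article does not say how large it would be.

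**Conclusion.** The concern holds in a limited form. As written, the main model understates the standard error whenever CAC is below 1. At the article's inputs the linear-model error rate runs from about 6% to 14% for an assumed CAC of 0.95 to 0.5. The binary primary outcome is likely to be somewhat milder, about 7% to 8% at CAC 0.8. The concern is greatest for outcomes with many records per practice and slight where records are few. These figures rest on an unknown CAC, equal record counts, an assumed 18/18 split and large-sample theory. This is a should-fix: a cheap improvement to the analysis, not proof that the primary test fails.

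**What to change.** In Statistical methods, for the outcomes from the record extracts (the primary outcome and secondary outcomes (i) and (ii)), replace the single practice effect with a practice random intercept plus a practice-by-timepoint random effect. Report both variance components. Add a sensitivity model with a random practice-level intervention effect, because the article expects practices to respond differently. Do not extend the requirement to the provider survey, where there may be too few respondents per practice to estimate the extra variance.

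The cost is one more variance component and an interval that is wider where practices do drift: a standard error of about 4.1 instead of 3.6 percentage points at CAC 0.8, 30 records and a 40% outcome. If CAC is near 1, little is lost. The extended model restores the nominal 5% in large-sample linear theory. No logistic results for it are reported here, so its convergence and error rate on binary data should be checked before it is fixed.

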## Methods

### Study design

This quality improvement programme has a mixed methods approach incorporating a cluster randomised controlled trial (cRCT) design with blind allocation to early and late intervention groups [19]. Quantitative measures collected cross-sectionally at multiple timepoints will be assessed using the recommended statistical approach for step-wedged cRCT designs [20]. An embedded qualitative component will explore the acceptability, usefulness and sustainability of the intervention(s).

The study will be informed by the literature on organisational change that identifies the factors influencing the diffusion and institutionalisation of organisational innovations, and where organisations are considered as a whole rather than as a set of independent attributes [21–23]. Two principles underpin the study design: a) Participatory research: where community based research partnerships built upon on-going knowledge exchange are considered an essential component of sustainable innovations and, community impact [24, 25]; and b) Implementation science: incorporating contemporary approaches to quality improvement, and, in particular Normalization Process Theory’s principles for understanding the process of embedding change in a practice by examining what people actually do and how they work [26].

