### Outcomes

The primary outcomes will be changes in number of claims for the delivery of Medicare Benefits Schedule (MBS) reimbursed comprehensive health assessments among patients identified as being from a refugee background. We will calculate the change in proportion of eligible (within 12 months of arrival in Australia) refugee background patients with medical records where there is evidence of billing for a comprehensive health assessment (MBS items 701, 703, 705 and 707). Secondary outcome measures will be:(i)The change in the proportion of patients with records with recorded refugee identification (country of birth, ethnicity, year of arrival).(ii)The change in proportion of refugee patient consultations with documented use of credentialed interpreter, where one was required.(iii)The change in practice staff knowledge, attitudes and behaviours towards referring refugee background patients to external health and welfare services for which their refugee patients are eligible.

We will also measure changes in general practitioners’ confidence to undertake health assessments, catch-up immunisation and infectious diseases screening, and changes in practice routines relating to health assessments.

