The following instruments will be used to collect data:Quantitative measures**De-identified data extraction**: The PENCS CAT4**™** tool, is widely used by practices and Primary Health Networks to monitor practice performance and inform routine quality improvement interventions. The research team designed an add-on software report within the CAT4**™** tool to allow measurement of general practice performance in key refugee health quality domains including refugee identification, interpreter use and health/mental health assessments. Searches of each participating practice’s electronic clinical and practice management software will first filter all patient records where identifiers of country of birth, ethnicity or language spoken that are relevant to refugee populations have been recorded in a coded field or as free text in the patient record. All identifiable information including patient name, address, contact details will be automatically removed prior to the output being made available to the researchers. This output will be a de-identified line listed excel spreadsheet that includes (where available) residential postcode, age, gender, country of birth, ethnicity, language spoken, year of arrival, interpreter needed, list of diagnoses, date of first visit, dates of visits in the last 12 months, dates of visits where an interpreter was used, date of last health assessment and date of last mental health care plan. This data extract will be carried out at baseline and repeated at the end of the intervention period as well as at 6-months post intervention completion. Analysis will allow us to identify track changes in practice performance as a result of the quality improvement intervention.A **Practice Description survey** (Additional file 2) will be administered to the practice team at baseline and will contain questions regarding a practice’s staffing, patient load and demographics, organisational structure/governance, appointment setting systems, clinical record management systems, payment systems and processes for client transition including transfer of information. Survey items were primarily derived from the Preventive Evidence into Practice study (PEP) [33] and the Canadian Community-Based Primary Health Care Common Indicator Project [36].**A Practitioner survey** (Additional file 3) will be administered to each consenting general practitioner. This will contain questions ascertaining practice staff’s background, experience and interest in refugee health care delivery, and experience of and attitude towards using interpreters in clinical care. Survey items were derived from the Comparison of Models of Primary Care in Ontario study [37]; PEP [33]; the Community-Based Primary Health Care Common Indicator Project [36]; and the Patient-Centered Medical Home Scale [38]. The survey will be repeated at the end of the intervention period.**A Refugee healthcare survey** (Additional file 4) will be administered to each practice and their staff participating in the project by the Research Officer during the first facilitation visit to document whole-of-practice approaches to refugee care. The survey items were designed specifically for this project, informed by the areas of focus emerging from the deliberative forum. The data generated by using this tool will also inform tailoring of the practice facilitation intervention. The survey will be repeated at the end of the intervention period.b)Qualitative data**Semi-structured interviews**: Following the intervention period, we will interview Practice Facilitators (*n* = 3), research officers (n = 3) and practice staff who played a key role in intervention from two practices in each round within each region (*n* = 12 practices) to explore their experiences of being involved in the intervention. The aims of the interviews are to identify key factors affecting the fidelity, effectiveness and sustainability of the intervention.**Facilitator diary:** Practice Facilitators will maintain a reflective diary of their contacts with practices to document activities undertaken, resources provided, challenges encountered and how these were overcome.**Action plans***:* As part of the intervention, Practice Facilitators will work alongside key practice personnel to document practice goals and relevant activities relating to refugee identification, interpreter use, conduct of comprehensive health assessments and referral. Action plans will be used to monitor progress towards practice goals and (where applicable) the documentary evidence of achieving these goals.**Facilitator meeting minutes***:* The research team will maintain detailed minutes from the research officers’ meeting and the Practice Facilitator meetings.**Reports of regional needs assessments***:* Will provide additional information on the region, including refugee population demographics, distribution general practice clinics and refugee health services within the catchment and socio-political factors affecting service provision.

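### Six-monthly extracts of patients who stay eligible for twelve months share patients, and the planned model covers neither that repetition nor practice-by-time variation, so its standard errors need not be nominal

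*Protocol article*

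**What the plan says.** All references are to the protocol article.

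- **Outcomes.** The denominator is "eligible (within 12 months of arrival in Australia) refugee background patients with medical records".
- **Data collection methods.** Early practices are measured at baseline, then "at 6-months (immediately after completion of the intervention), and at 12 months (6-months after the intervention has been completed"). Late practices have one further pre-intervention extract. Each search will "first filter all patient records where identifiers of country of birth, ethnicity or language spoken that are relevant to refugee populations" have been recorded. No fresh sample is drawn, and nobody already counted is removed. The output includes "date of last health assessment and date of last mental health care plan". No patient key is among the listed fields.
- **Study design.** The analysis is described as one of "Quantitative measures collected cross-sectionally at multiple timepoints".
- **Sample size.** Each clinic is to supply "cross-sectional data from 30 refugee background patients at each timepoint".
- **Statistical methods.** Fixed effects are group, intervention status and categorical timepoint. If practice-level clustering is found, "the mixed models will include a cluster-specific random effect to deal with clustering at the practice level". If it is not significant, single-level regression may be used. No other random effect is named.

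**The concern.** A patient who arrived within six months before one extract is normally still inside the 12-month window at the next, so the same people enter consecutive extracts. Because the outcome is read from the date of the last assessment, someone counted as assessed at one extract will normally still count as assessed at the next. Their two outcomes are positively correlated beyond what they share with other patients of the practice.

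A constant practice intercept represents only correlation that is common to all patients of a practice and the same at every pair of timepoints. It omits two things:

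- the extra correlation of a patient seen twice;
- practice effects that move over time, which is plausible when the intervention sets out to change practice routines.

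The two omissions act in opposite directions on the standard error of the intervention effect. At stake is whether confidence intervals and p-values for the primary outcome have their stated coverage and error rate.

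**Working it through.** **The plan's own figure.** The sample size section gives about 12 clinics per region but no baseline proportion, so it can be neither confirmed nor refuted. For 12 clinics, 30 patients and two timepoints, a rise of 25 to 30 percentage points gives power 0.97 to 1.00 over baselines of 5 to 50%. Read as a relative rise from an assumed 60% baseline, it gives 0.69 to 0.85. The point below does not depend on that figure.

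**Step 1: overlap.** At month t the eligible patients arrived in (t−12, t]. At t+6 they arrived in (t−6, t+6]. The shared arrivals are (t−6, t], so with steady arrivals the overlap is 6/12 = 50% between adjacent extracts and 0% between extracts 12 months apart. The listed extract fields hold only the year of arrival, so the window may be coarser in practice.

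**Step 2: inputs.**
- From the document: 36 practices (taken as 18 + 18), m = 30, ICC = 0.05, early practices at timepoints 0–2, late practices at 0–3.
- Assumed: proportion 30%, overlap o = 0.5, within-patient correlation net of practice r = 0.3, 0.5 or 0.7, cluster autocorrelation c = 1, 0.8 or 0.6.

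**Step 3: variances (linear approximation on practice-by-timepoint means).**
- Total: 0.30 × 0.70 = 0.21.
- Practice: τ² = 0.05 × 0.21 = 0.0105.
- Within practice: σ² = 0.1995, and σ²/m = 0.1995/30 = 0.00665.
- Planned model W: diagonal 0.0105 + 0.00665 = 0.01715; every off-diagonal 0.0105.
- True covariance V: same diagonal; off-diagonal c × 0.0105, plus o × r × 0.00665 for adjacent extracts. At o = r = 0.5 the addition is 0.25 × 0.00665 = 0.00166.

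**Step 4: standard errors of the intervention effect.** With A = ΣX′W⁻¹X over practices, the model variance is A⁻¹ and the true variance of the same estimator is A⁻¹(ΣX′W⁻¹VW⁻¹X)A⁻¹. The model SE is 3.33 points throughout.

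| Overlap | Autocorrelation c | r | True SE (points) | Model SE / true SE |
|---|---|---|---|---|
| 0.5 | 1 | 0.3 | 2.98 | 1.12 |
| 0.5 | 1 | 0.5 | 2.72 | 1.22 |
| 0.5 | 1 | 0.7 | 2.43 | 1.37 |
| 0 | 0.8 | – | 3.82 | 0.87 |
| 0.5 | 0.8 | 0.3 | 3.52 | 0.95 |
| 0.5 | 0.8 | 0.5 | 3.30 | 1.01 |
| 0.5 | 0.8 | 0.7 | 3.07 | 1.09 |
| 0.5 | 0.6 | 0.3 | 3.98 | 0.84 |
| 0.5 | 0.6 | 0.5 | 3.79 | 0.88 |
| 0.5 | 0.6 | 0.7 | 3.59 | 0.93 |

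Halving the overlap to 25% gives ratios of 1.05 to 1.14 at c = 1 and 0.91 to 0.96 at c = 0.8.

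**Step 5: error rate.** Actual two-sided type I error is 2Φ(−1.96 × ratio):
- overlap alone: 0.028, 0.016 and 0.007 at r = 0.3, 0.5 and 0.7;
- autocorrelation 0.8 alone: 0.088;
- autocorrelation 0.6 with overlap: 0.10 to 0.07.

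**Step 6: how large r might be.** For a state that persists once reached, with proportion a at the first extract and b at the second, r = √[a(1−b)/(b(1−a))]. Reading the planned rise as 30 points, 10→40%, 20→50% and 30→60% give 0.41, 0.50 and 0.53. Smaller rises give higher values. The document fixes neither a nor b, hence the range 0.3 to 0.7.

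**The case against.** **The article is condensed, and a separate analysis plan may hold the covariance structure.** Fair in part: naming a practice effect does not strictly exclude others. But the article sets out the main model's fixed effects and timepoint coding in full, makes the practice effect conditional, and twice describes the data as cross-sectional. That is a stated analysis that does not fit the stated sampling, rather than an omitted detail.

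**The two omissions may nearly cancel.** This stands. With 50% overlap and autocorrelation 0.8 the planned SE is within about 10% of the true one.

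**A reader might infer that repeated patients inflate the type I error.** They do not here. The intervention effect is partly a within-practice contrast, so with stable practice effects the overlap makes the reported SE too large. Inflation would come from practice effects that drift.

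**A reader might equally take 37% as the size of the error.** That is one end of an assumed range, needing r = 0.7 and no drift. Repeated patients are the newest arrivals, with least time to have been assessed at the first extract, which argues for a lower r.

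**Power may not suffer.** If the planned 25 to 30% is in percentage points, 25/3.33 is about 7.5 standard errors and power is not a concern. If it is relative to an assumed 30% proportion, the effect is 7.5 to 9 points and the loss is real. With overlap alone at r = 0.5, rejection needs 1.96 × 3.33 = 6.53 points. Power at 7.5 points is then Φ((7.5 − 6.53)/2.72) ≈ 0.64, against Φ(7.5/2.72 − 1.96) ≈ 0.79 with a correct SE.

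**Conclusion.** The concern holds as a mismatch between sampling and model. The overlap follows from the article's own eligibility window, extract spacing and whole-practice search; only the figure of one half needs the steady-arrivals assumption. The named model allows for neither repeated patients nor practice-by-time variation, so nominal coverage and error rate are not assured for the primary outcome.

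Over the combinations in the main table the reported SE lies between 0.84 and 1.37 times the true SE. Overlap, within-patient correlation, autocorrelation and the 30% proportion are all assumed, and the calculation is a linear approximation. The documents therefore do not support a claim that the intervals are definitely too wide or definitely too narrow. The correction is worth making because the direction cannot be known in advance and a remedy exists that does not require knowing it.

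**What to change.** Amend the main analysis in Statistical methods for the primary outcome:

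1. Retain the practice random effect whatever the clustering test shows, and drop the single-level alternative.
2. Add a practice-by-timepoint random effect.
3. Base confidence intervals and p-values on standard errors clustered by practice, with a small-sample correction suited to 36 practices. These allow for any correlation within a practice, including repeated patients, without linking records.
4. State that consecutive extracts share patients, instead of calling them simply cross-sectional.
5. Add a patient random intercept nested in practice only if the extracts already hold a pseudonymous key.

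Items 1 to 4 change analysis wording only. The price is some loss of efficiency or slightly wider intervals. A new key should not be relied on: Table 3 puts the late group's thirteenth month at March 2019, before the June 2019 publication, so many extracts were scheduled to exist already, and a protocol amendment would need approval from the ethics committees.
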